## 4.4 Sample Size

### 4.4.1 Villages

We estimated the sample size requirements for our two-by-two factorial design using simulation. Briefly, we generated simulated data assuming the alternative hypothesis and determined the sample size needed for how often (selecting 80%, our desired power) our statistical

test would yield a rejection of the null hypothesis. We adopt a non-inferiority design for each factor with non-inferiority limits of 8%. Assuming a standard deviation of 0.05 within each arm, a correlation of 0.5 between baseline and 36 month results (derived from previous studies), and no interaction between factors, we estimate that a total of 32 communities provides greater than 80% power for each main effect (95% one-sided non-inferiority). Thus, for Tanzania, out of a total of 32 villages, 16 villages will be assigned to annual treatment and 16 to a stoppage rule. We expect that between 40% and 80% of communities randomized to the stopping rule arm in The Gambia and Tanzania will stop mass treatment after one or two rounds, based on previous work. For Niger and the Gambia, the smaller community sizes imply a higher variance. Conservatively, we assumed the variance was one third higher. Thus, to obtain greater than 80% power, we require 12 villages in each arm (for a total of 48 villages, again assuming a one-sided 95% non-inferiority comparison with limit 0.08). Neither the assumption of plausible variation in the interaction effect nor the assumption of a beta distribution rather than a normal distribution alters these estimates to any substantial degree.

In Niger, the sample size provides sufficient power to distinguish between the expected prevalence of annual and biannual treatment arms (approximately 10% and 1% respectively based on mathematical projections), and for all countries, between the expected prevalence after 3 annual treatments with greater than 90% coverage versus 3 annual treatments with 80%-90% coverage (approximately 2% and 13% respectively based on mathematical projections). Note that we will be able to conduct a standard superiority test with a power of at least 80% to detect a difference of 0.08 for each main effect, as determined by simulation.) In practice, we have elected to enroll 12 grappes in each of the 4 arms.

We show the sample size for each hypothesis and assumption, recognizing the simple approach requested is not the analytic plan, and show that the simulation approach yields comparable estimates, and which includes consideration for our approach to analyses.

### **1) What are differences at 3 years post baseline in rates of trachoma and ocular *Chlamydia trachomatis* in communities randomized to mass antibiotic coverage of low (80-89%) versus high ( $\geq 90\%$ ) coverage.**

*We hypothesize that higher coverage (as measured in ages <10 years) will result in lower prevalence of infection at three years in all countries.*

In principle, this could be addressed by a two-sample T-test. We estimate that the inclusion of 12 communities per arm in both The Gambia and Niger will provide greater than 80% power to detect a 6% difference in the prevalence of infection in individuals 0 to 5 years of age at 36 months, assuming a standard deviation of 5.0% and a two-tailed alpha of 0.05.

We computed the sample sizes for two-sample T-tests by finding solving the following standard equation for  $n$ :

---

 Snapinn SM. 2000. Noninferiority trials. Current Controlled Trials in Cardiovascular Medicine 1:19-21

$$\Psi_{2n-2}\left(t_{\alpha/2, 2n-2}, \frac{|\delta|\sqrt{n}}{\sigma\sqrt{2}}\right) = \beta \text{ (Chow et al, 2003)},$$

where sigma divided by the square root of n is the standard deviation (alpha=0.05), delta is the effect size, 1-beta is the power,  $\Psi_m(x, k)$  denotes the cumulative distribution function of the non-central T-distribution with m degrees of freedom and non-centrality parameter k, and  $t_{a,m}$  is the ath quantile of the T-distribution with m degrees of freedom and non-centrality parameter k, and  $t_{a,m}$  is the ath quantile of the T-distribution with m degrees of freedom.

We will randomize 12 communities into each cell of the factorial design described below. We used the standard deviation found from the distribution of infection rates in Niger of communities of the size that are proposed for Niger and The Gambia. When we examine the distribution of infection rates in Niger of larger communities, the standard deviation drops to 4%. Thus, we estimate that the inclusion of 8 of the larger Tanzanian communities per arm will provide approximately 80% power to detect a 6% difference in the prevalence of infection in individuals 0 to 5 years of age at 36 months, assuming a standard deviation of 4.0%. This computation was conducted using the same formula as above. We will randomize 8 communities from Tanzania into each cell of the factorial design described below. We have used our judgment to propose that a 6% difference in the prevalence of infection is the clinically relevant difference we wish to detect. After three years of mass treatment, we expect infection rates to be low, and the difference in terms of re-emergence between, for example, 2% and 7% is insignificant. Similarly, re-emergence rates may be higher, but we do not expect differences in the rates, if at three years infection rates are 10% to 15%. Note that the community size in Tanzania is now between 1,000-2,000 persons, at least 1.5 times the size of Niger (300) or The Gambia (600-800).

## **2) What are the differences at 3 years post baseline in the rate of ocular *C.trachomatis* in communities randomized to mass antibiotic treatment of children every 6 months versus yearly treatment of everyone? (Niger only)**

*We hypothesize that treatment of children every six months will result in a lower prevalence of chlamydial infection at three years in Niger compared to yearly treatment of all residents.*

As with Hypothesis 1, this could be addressed by a two-sample T-test. We estimate that the inclusion of 12 communities per arm in Niger will provide greater than 80% power to detect a 6% difference in the prevalence of infection in individuals 0 to 5 years of age at 36 months, assuming a standard deviation of 5.0% and a two-tailed alpha of 0.05. This computation was conducted using the same computation as for Hypothesis 1.

## **3) What are differences at 3 years post baseline in rates of trachoma and ocular *C. trachomatis* in communities randomized to yearly mass antibiotic treatment versus a strategy to discontinue treatment (graduate communities), if infection/disease reaches less than 5%? (Tanzania and The Gambia only)**

---

*We hypothesize that the prevalence rates of infection, trachoma will be no different in villages treated for three years versus villages in the arm with the graduation rule at three years in Tanzania and the Gambia.*

Here we use a non-inferiority analysis. A total of 8.06 Tanzanian communities is needed to allow the null hypothesis that the graduation rule is at least 6% inferior to be rejected with a power of greater than 80% using a 2-sided alpha of 5%, and assuming a standard deviation in the 36-month prevalence of 4%. This computation was conducted using the same formula as in hypothesis 1 (see Chow et al, sec. 4.4.1). Note that with a one-sided test with an alpha of 0.05, 80% power is achieved with 7 Tanzanian communities.

A total of 11.9 Gambian communities is needed to allow the null hypothesis that the graduation rule is at least 6% inferior to be rejected with a power of greater than 80% using a 2-sided alpha of 5%, and assuming a standard deviation in the 36-month prevalence of 5%. As before, we used the same formula as in hypothesis 1. For a one-sided test, 80% power is achieved with 10 communities.

We originally computed the sample size for an 8% limit to be considered non-inferior; because for this hypothesis we felt the data would show very low rates of infection (in order to be graduated, the estimate for a community must be 0%) and 6%-7% infection rates at this level would not result in significant re-emergence. However, for consistency sake, we show that we do have 80% power (as opposed to 90% power to detect 8% differences) with the sample size as justified to detect differences as low as 6%.

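### The 80% power for 6 points in Protocol 4.4.1 belongs to one factorial cell against another; the stated main-effect comparisons in Tanzania and Niger have about 98%, and per-group numbers are printed as totals.

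*Protocol*

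**What the plan says.** Section 4.4.1 of the Protocol contains two sets of calculations.

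The first is a simulation for the factorial design. It uses a non-inferiority limit of 8 points for each factor, one-sided 95% confidence, SD 0.05, a baseline-to-36-month correlation of 0.5 and no interaction. Its power statement is for main effects, and for Tanzania it spells out the split: "out of a total of 32 villages, 16 villages will be assigned to annual treatment and 16 to a stoppage rule". For the smaller communities of Niger and The Gambia the variance is raised by one third, and the text concludes that "to obtain greater than 80% power, we require 12 villages in each arm", 48 in all.

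The second is a set of two-sample t-test calculations, one per hypothesis, with a 6-point difference:
- Hypothesis 1, Niger and The Gambia: 12 per arm for more than 80% power, "assuming a standard deviation of 5.0% and a two-tailed alpha of 0.05".
- Hypothesis 1, Tanzania: "we estimate that the inclusion of 8 of the larger Tanzanian communities per arm will provide approximately 80% power to detect a 6% difference", with SD 4%.
- Hypothesis 3, Tanzania: 8.06 communities, described as a total, "using a 2-sided alpha of 5%, and assuming a standard deviation in the 36-month prevalence of 4"%. Also, "with a one-sided test with an alpha of 0.05, 80% power is achieved with 7 Tanzanian communities".
- Hypothesis 3, The Gambia: 11.9 communities, again described as a total, "using a 2-sided alpha of 5%, and assuming a standard deviation in the 36-month prevalence of 5"%. The one-sided number is 10.
- Hypothesis 3, summary: "we do have 80% power (as opposed to 90% power to detect 8% differences) with the sample size as justified".

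Under hypothesis 1 the same 8 and 12 are given as the number of communities in each cell of the factorial design. Section 1.3 defines the primary comparisons as high against low coverage and one frequency strategy against the other. Sections 1.3 and 4.1 give a minimum of 16 communities in each arm.

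**The concern.** The word arm means a factor level in sections 1.3 and 4.1 but a cell in most of 4.4.1. A number computed per compared group was then allocated per cell, so the 80% is attached to a comparison half the size of the one the protocol calls primary. Hypothesis 3 adds a second slip, calling a per-group number a total.

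What is at stake is how the trial's resolution is described. A reader or the DSMC would take 6 points as roughly the smallest difference the main comparisons can detect with 80% power, and would take 12 per cell as the minimum that 80% power demands. Neither follows from the stated inputs. Read literally, the totals also halve the number of communities that the hypothesis 3 calculation needs.

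**Working it through.** **Formula.** The one printed under hypothesis 1: power = 1 − Ψ(t; 2n−2, λ), with n communities per compared group, critical value t on 2n−2 degrees of freedom, and non-centrality λ = δ√n/(σ√2). For non-inferiority the same formula applies with true difference 0 and δ as the margin.

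**Step 1: reproduce the printed sizes.** Solve for n at 80% power with δ = 6.

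| SD | Test | n per compared group | Printed |
|---|---|---|---|
| 4 | two-sided 5% | 8.06 | 8.06 |
| 5 | two-sided 5% | 11.94 | 11.9 |
| 4 | one-sided 5% | 6.30, so 7 | 7 |
| 5 | one-sided 5% | 9.34, so 10 | 10 |

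The arithmetic is right. Because n is per compared group, the two-group totals are 2 × 8.06 = 16.1 and 2 × 11.94 = 23.9, or about 17 and 24.

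**Step 2: identify the comparison.** Two-sided 5%, δ = 6.

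| Comparison | SD | λ | Power |
|---|---|---|---|
| 8 v 8 (one Tanzanian cell against one) | 4 | 6√8/(4√2) = 3.00 | 79.7% |
| 16 v 16 (Tanzania, factor levels) | 4 | 6√16/(4√2) = 4.24 | 98.4% |
| 12 v 12 (one Niger cell against one) | 5 | 6√12/(5√2) = 2.94 | 80.2% |
| 24 v 24 (Niger, factor levels) | 5 | 6√24/(5√2) = 4.16 | 98.3% |

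The printed 80% is the cell comparison. Using the degrees of freedom of a four-cell model (2n−4) changes the main-effect results only to 98.4% and 98.2%.

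**Step 3: difference detectable with 80% power, main effect.** 4.09 points in Tanzania (16 v 16, SD 4) and 4.13 points in Niger (24 v 24, SD 5).

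**Step 4: the requirement of 12 per cell.** Inputs from the opening of 4.4.1: margin 8, one-sided 5%, variance one third higher, so SD = 5 × √(4/3) = 5.77.
- Without baseline adjustment, 80% power needs n = 7.22, so 8 per factor level.
- With the stated correlation of 0.5, the residual SD is 5.77 × √(1 − 0.25) = 5.0 and n = 5.65, so 6 per factor level.
- The 24 per factor level actually planned gives 99.9% even without adjustment. For Tanzania, 16 per level at SD 5 gives 99.7%.

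**Step 5: the 90% for 8 points.**

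| Comparison, δ = 8 | SD | Test | Power |
|---|---|---|---|
| 12 v 12 | 5.77 | two-sided 5% | 90.0% |
| 8 v 8 | 5 | one-sided 5% | 91.9% |
| 8 v 8 | 4 | two-sided 5% | 96.0% |
| 12 v 12 | 5 | two-sided 5% | 96.3% |

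The 90% therefore reproduces as a cell comparison with the inflated variance from the opening of 4.4.1. With the SDs used under hypothesis 3 it would be about 96%.

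**The case against.** The best reply is that nothing here endangers the trial. The sizes reproduce exactly, the misattribution understates power, and statements of more than 80% or at least 80% stay true for Tanzania and Niger. Section 4.4.1 itself says that the simple formula is not the analysis plan, and it says of Niger that 12 per cell was a choice in practice, which softens the word require. A cell comparison also has a place in the protocol. One expected-prevalence contrast in 4.4.1 is three annual treatments at high against low coverage. Section 16.1.1 expects a possible interaction and defines the coverage coefficient as the effect of high coverage alone. Planning conservatively for simple effects is defensible.

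All of that stands, and it limits the point to labelling and restatement. It does not remove the point. The simulation is offered as giving estimates comparable to the t-test, yet it is described for main effects with no interaction, where its inputs give 99.7% or more. The statements of approximately 80%, of having 80% power, of totals needed and of 12 per arm being required do misdescribe that comparison.

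A reader might infer more than the documents support:
- That the power arithmetic is wrong or the main effects underpowered. Steps 1 and 2 show the opposite.
- That the 90% figure is an error. It reproduces at 12 v 12 with the variance one third higher, two-sided; what is missing is a statement of those inputs, since the opening of 4.4.1 describes a one-sided test.
- That The Gambia also has 98% at 24 v 24. Section 4.3.3 assigns whole districts, one per cell, so its enumeration areas are not independently randomized and the figure does not transfer.
- That fewer communities should be enrolled. The protocol judges 6 points to be the relevant difference and does not commit to 80% as a ceiling.

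**Conclusion.** The point holds as a misattribution of correctly computed figures. The 80% power for 6 points is for one factor within one level of the other. The stated main-effect comparisons have about 98% power for 6 points, some 18 percentage points more, and reach 80% power at about 4.1 points. The numbers called totals under hypothesis 3 are per compared group, and 12 per cell (24 per factor level) is well above the 8, or 6 with the correlation, per factor level that 80% main-effect power needs under the stated inputs.

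This rests on the protocol's SDs of 4% and 5%, communities randomized independently within Tanzania and Niger, no interaction between the factors, and the t-test as an approximation. Section 16.1.1 names a Wilcoxon test for cross-sectional comparisons, and 16.2.4 names a baseline-adjusted linear model for Niger, so the exact power of the planned analyses will differ somewhat. If the factors interact and simple effects are what is read, the cell-level 80% is the relevant figure. The error is conservative and leaves the validity of the comparisons untouched.

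**What to change.** Revise the text of 4.4.1; enrolment, randomization and procedures do not change.

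1. Label the 8 v 8 and 12 v 12 results as per cell, giving power for the effect of one factor within one level of the other, and use separate words for cell and factor level throughout.
2. Under hypothesis 3, describe 8.06 and 11.9 as communities per compared group instead of totals.
3. State main-effect power separately for Tanzania (16 v 16) and Niger (24 v 24): about 98% for 6 points and 80% at about 4.1 points, by the t-test approximation and assuming no interaction.
4. Replace the statement that 12 villages per arm are required with one saying that 12 per cell was chosen and exceeds what 80% main-effect power needs under the stated inputs (about 8 per factor level, or 6 with the 0.5 correlation).
5. Keep the 90% figure for 8 points, but state that it is a cell comparison at 12 v 12 with the variance one third higher, two-sided. With the hypothesis 3 SDs it would be about 96%.
6. Say that the 24 v 24 figure does not apply to The Gambia, and describe that country's power separately in light of the district-level assignment in 4.3.3.

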#### **4.4.2 Children**

We chose a sample size of 100 children per community specifically for the Tanzanian and Gambian arms, where we need sufficient numbers of children to determine with precision if disease has fallen to less than 5%. At the same time, we balanced concerns for costs and survey difficulties if this methodology is to be used by country programs to decide if mass treatment can be stopped. With 100 children in the sample, if zero children have infection, the upper 95% confidence limit of the estimated prevalence is less than 5% (3%). For example, if one child in the sample has infection, then mass treatment will not be stopped, even though the estimate of the mean is 1%, as we cannot be 95% certain that the true prevalence is not above 5%. We cannot power the study for infection below 1%, as that would require over 3 times the sample size (368 children), and such a size would be prohibitively expensive in terms of laboratory testing and follow-up time. However, with our sample size of 100 if even one child has infection, we know the estimate is 1% with a 95% upper confidence bound of 5.4%. We recognize this is a conservative approach, but we are strengthening the likelihood that the true value is below 5% according to the upper confidence limit.

---

 Feiveson AH. 2002. Power by simulation. STATA Journal 2:107-124

## Chapter 5: Eligibility, Consent and Enrollment

### 5.1 Eligible Communities

This study aims to determine the impact of different approaches to mass treatment on prevalence of trachoma and infection in villages that are hyperendemic, mesoendemic, and hypo-endemic for trachoma. Within each country, there may be communities that may fall into each category, but in general the hyperendemic communities will be located in Niger, the mesoendemic communities in Tanzania, and the hypo-endemic villages in The Gambia, based on previous surveys. Eligible communities for each country are described below:

To be eligible for the trial in Niger, a community must meet the following criteria:

1. The community must be located in the target district around Matameye
2. The village chief consents to participation in the trial (this does not obviate the need for individual consent, but without overall leadership consent, the community as a whole cannot be part of the trial)
3. The prevalence of TF/TI in the community must be  $>10.5\%$ .
4. Communities must be more than four kilometers away from the center of any semi-urban areas, which are thought to have a lower prevalence of trachoma
5. Communities must have an estimated population of between 250-600 people.

To be eligible for the trial in Tanzania, a community must meet the following criteria:

1. The community must be located in the Kongwa District
2. The community leadership gives consent that the mtaa is willing to participate in the trial (this does not obviate the need for individual consent, but without overall leadership consent, the community as a whole cannot be part of the trial)
3. The estimate of the village prevalence of trachoma is 20% or greater in preschool age children. For Tanzania, we want to concentrate on trachoma endemicity that is not at the level of virtual elimination, as we will have ample numbers of communities from The Gambia that fall into this range.
4. If the population estimate from the last Tanzania census for the community is greater than 5,000 persons, the village is not included. This will effectively exclude Kongwa town and two large communities on the main road. We excluded them because the need to do census updates and mass treatment in these communities will consume excessive time for our team. If the population estimate for an mtaa is less than 1,000 persons, and it geographically cannot be combined with another mtaa, it is excluded.

To be eligible for the trial in The Gambia, an EA must meet the following criteria:

1. The EA must be located in the target districts
2. Where several villages are contained within the EA, each village leadership gives consent that the village is willing to participate in the trial (this does not obviate the need for individual consent, but without overall leadership consent, the village as a whole cannot be part of the trial)
3. Where the EA consists of a single village or a segment of a large community, consent is obtained from the community leadership (note that no village is larger than 4,000 persons or 6 EAs)
4. The EA must have a prevalence of trachoma greater than 5%.

We will use the best available data on prevalence prior to the baseline surveys to determine eligibility. Once the communities are randomized, and the baseline survey completed, if a community is not eligible on the basis of trachoma rates, then another community is chosen for that arm from the alternate list.

## 5.2 Eligible Children

Within each community, sentinel children will be randomly selected to serve as indices of the village rate of trachoma and ocular *C. trachomatis* infection. For each country, the eligibility criteria are identical. In order to be eligible to be a sentinel child, the child must meet the following criteria:

1. The child is age 5 years or younger
2. The child must be a resident in an eligible, sample community (defined as either living in the community since birth, or moved in with parents or guardians).
3. The child must not have an ocular condition that would preclude grading trachoma or taking an ocular specimen.
4. The child must be willing to have a swab taken as part of being a sentinel child (this is critical for The Gambia and Tanzania, as each swab result counts towards meeting the stopping rule)
5. The child must have an identifiable guardian capable of providing consent to participate.

While ideally, we would only wish to select one child per household, in locations with smaller communities, we may have no choice but to select more than one child per household. Therefore, we have not restricted the number of children who may participate per household. We discuss the need to adjust for household clustering in the analyses.

## 5.3 Consent Procedures

Procedures for gaining consent to conduct this project vary in each country, depending on the requirements in Niger, The Gambia, and Tanzania.

